## 2) Objectives\*

The goal of the proposed application is to evaluate in an effectiveness-implementation type I hybrid trial, an enhanced version of eHealth Familias Unidas for reducing depressive, anxious symptoms and suicide behavior in Hispanic youth. Using a randomized rollout design of 18 clinics, the study's aims are to:

**AIM 1:** Evaluate the effectiveness of eHealth Familias Unidas for Mental Health in preventing/reducing depressive, anxiety symptoms; suicide ideation and behavior; and drug misuse among those with poor family communication, elevated levels of depressive or anxiety symptoms, or a history of suicide ideation or behavior.

**H1:** eHealth Familias Unidas for Mental Health will be effective, relative to standard of care, in reducing these outcomes in Hispanic adolescents over time.

**AIM 2:** Determine whether intervention effects are partially mediated by family communication and externalizing behaviors, including drug misuse, and moderated by parental depression.

**H2:** Intervention effects on mental health outcomes will be partially mediated by improvements in family communication, externalizing behaviors (including drug misuse) and moderated by parental depression.

**Exploratory AIM 3:** Intervention impact on mental health and drug misuse as well as sustainment of the intervention in clinics will vary by quality of implementation at clinic and clinician levels.

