## 7) **Data Management\***

*Data Management & Quality Control Procedures.* Assessment data will be entered directly by participants onto tablets via REDCap, which is linked to secure university servers. We will follow procedures to ensure quality control in the collection, verification, and documentation of data that we established in previous trials. Data files will be exported from REDCap, will be cleaned and reviewed, and prepared for analysis with analysis programs, including *Mplus*.

*Data Preparation & Preliminary Analyses.* Testing of distributional assumptions will include statistical tests for univariate and multivariate normality (tests of skew & kurtosis) as well as visual inspections of the empirical distributions for the data at each time point. Should deviations be deemed sufficient for concern, transformation of variables will be attempted where possible. The distribution of our outcomes will be skewed, and methods specifically used for such data will be used. Often such data follow a Poisson distribution, and a Poisson regression or a two part growth curve model would be the appropriate way to handle these analyses in the event of positively skewed distributions. Reliability estimates of internal consistency (Cronbach's  $\alpha$ ) will be generated for all scale scores. If reliability estimates are found to be below .80, item total correlations and factor analyses will be employed to diagnose and correct psychometric problems. To account for multiplicity adjustments in the proposed analyses below, we will sensitive analyses for primary outcomes.

**AIM 1:** Evaluate the effectiveness of eHealth Familias Unidas for Mental Health in preventing/reducing depressive, anxiety symptoms; suicide ideation and behavior; and drug misuse among those with poor family communication, elevated levels of depressive or anxiety symptoms, or a history of suicide ideation or behavior.

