For continuous measures of depressive and anxious symptoms and drug misuse, we will analyze impact using growth modeling with four time points modeled as a multivariate normal distribution. For suicide behavior (i.e., ideation and attempt), and drug misuse, we will conduct generalized growth modeling with mixed effects using these repeated binary measures. For both continuous and binary outcomes, our analytical procedures will follow those we have used previously to analyze Familias Unidas trial data. For our standard analyses we will use *Mplus* to examine changes in growth using its two-level modeling of clinic and individual, commonly called three-level modeling in the mixed effect modeling literature (individuals with repeated measures nested within clinics,). Since youth are recruited from all 18 clinics both during Control and eHealth Familias Unidas Mental Health, we can consider clinic to be a “blocking

factor,” so the overall effect is essentially a mean of the differences in response across all 18 clinics. After suitable transformation of the time axis, handling of missing data, and model fit checking (see Clinical Trials Section 4B for additional details), we will use a Wald type test on the difference in mean slope parameters for eHealth Familias Unidas versus Control assigned participants. Base rates for suicide attempts are low and thus we accounted for them in our analytic plan and power analyses (see below). In a universal trial of Familias Unidas, found that at baseline 9.2% of youth reported suicide ideation and 5.7% reported a suicide attempt in the preceding year. We have presented power analyses below based on these low but not insignificant rates. Finally, to ensure that our final timepoint which has a longer time gap does not overly influence the findings, we will examine transformations of the time axis.

**AIM 2:** Determine whether intervention effects are partially mediated by family communication and externalizing behaviors, including drug misuse, and moderated by parental depression.

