**Power Analyses:** For continuous effectiveness outcomes, such as the slope of depressive symptoms over the 18 months, we have 87% power to detect an effect size of 0.5 (Type I error 0.05), which is the median effect size we found in a previous synthesis project investigating reduced depressive symptoms in 19 prevention programs with a two year follow-up (see Figure 5 in the following reference). We expect this effect size given that we are now including youth who are elevated on depressive or anxiety symptoms or have a history of suicide ideation or attempts. For suicide ideation, our growth models for repeated binary measures indicates we will have over 70% power to detect a yearly odds ratio (OR) reduction of 0.50 when the prevalence of ideation at baseline is 0.12 (or 12%). For suicide attempts, the baseline prevalence we have observed previously is 0.086 (or 8.6%), and this provides 55% power to detect an OR of 0.5. These ORs and prevalence rates were taken from our most recent Familias Unidas trials using the subset of youth with poor family communication, matching our inclusion criteria. For suicide attempts, if we obtain an OR of 0.4, we would have 71% power to detect this change from baseline for attempts and 88% power for ideation. We will analyze impact on K-CAT MDD as well as use missing data and a two-stage design to calibrate these findings against K-SADS MDD, see section 4.4.). Thus, we have sufficient power to detect a large effect on suicide outcomes over time. For the power of detecting a mediation effect, we take as an example 6-month family communication mediating 18-month depressive symptoms. If both the a and b estimators have 80% power of rejecting their nulls, then the product has a 64% power of rejecting the mediation pathway as being significant. If each a and b estimators have 85% power, the product has 72% power of rejection. Additional details are provided in Clinical Trials Section 4B.

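### H1 rests on five unranked outcomes with multiplicity left to a sensitivity analysis, and drug misuse is assigned two models with neither named as deciding

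*Protocol*

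**What the plan says.** Section 2 (Objectives) sets Aim 1 as "preventing/reducing depressive, anxiety symptoms; suicide ideation and behavior; and drug misuse" in the eligible youth. H1 states that the intervention "will be effective, relative to standard of care, in reducing these outcomes in Hispanic adolescents over time". The Aim 1 analysis text in section 7 treats suicide behaviour as ideation and attempt, so H1 spans five outcomes. They are not ranked, and nothing says whether one, some or all must succeed.

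The paragraph on data preparation in section 7 deals with multiplicity in one sentence: "To account for multiplicity adjustments in the proposed analyses below, we will sensitive analyses for primary outcomes". A verb is missing, no method is given, and the primary outcomes are not identified there or elsewhere in the protocol.

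The Aim 1 analysis text assigns drug misuse twice. One sentence reads "For continuous measures of depressive and anxious symptoms and drug misuse, we will analyze impact using growth modeling", with the four time points treated as multivariate normal. The next places suicide behaviour together with drug misuse in a different model: "and drug misuse, we will conduct generalized growth modeling with mixed effects using these repeated binary measures". The data-preparation paragraph expects the outcomes to be skewed and adds: "Often such data follow a Poisson distribution, and a Poisson regression" or a two-part growth curve model would then be appropriate.

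The Power Analyses paragraph gives a type I error once, for continuous outcomes: "we have 87% power to detect an effect size of 0.5 (Type I error 0.05". It gives no alpha for the suicide outcomes and no power for drug misuse.

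**The concern.** A sensitivity analysis shows whether a conclusion would survive adjustment. It does not limit the error rate of the tests from which the conclusion is drawn. With five unranked outcomes and no decision rule, a positive result on one of them could be reported as support for H1, and the error rate of that claim would be well above 5%.

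For drug misuse there is a second route. A difference in slope on a continuous score and a difference in slope on the log-odds of any use are different quantities and can disagree. If neither is named as deciding, the choice can be made after both results are known. The normal model is also the harder one to defend, because the same section expects skew.

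**Working it through.** **The protocol's own figure.** No familywise error rate is stated, so there is none to reproduce. The stated 87% power cannot be rebuilt, because the intraclass correlation, slope variance and time coding are not given. A plain two-sample test with 234 per condition (468/2, an assumption) gives 99.97%. Power of 87% corresponds to about 77 effective youth per condition, a design effect of 234/77 = 3.04. At 468/18 = 26 youth per clinic that means an intraclass correlation of (3.04 − 1)/25 = 0.08. Nothing here shows the 87% to be wrong. It is used below as stated.

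**Familywise error across H1.** Inputs: k = 5 outcomes (section 2); two-sided 0.05 for each test (inferred); success on any one outcome supports H1 (assumed).

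- Independent tests: 1 − 0.95^5 = 0.226.
- Equicorrelated normal test statistics, simulated with 1,000,000 draws: 20.8% at correlation 0.3, 18.2% at 0.5 and 14.8% at 0.7.
- Upper bound under any dependence: 5 × 0.05 = 25%.

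The protocol gives no correlation between the outcomes, so the range is shown.

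**The other reading of H1.** If all five outcomes must succeed, familywise error is not inflated. The power to establish H1 then cannot exceed the lowest component power, which at the planning odds ratio of 0.5 is at most the 55% stated for attempts. The two readings lead to very different trials, and the text does not choose between them.

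**Picking between the two drug-misuse models.** Taking the better of two two-sided 0.05 tests gives a type I error of 9.1% if the test statistics correlate 0.5, 8.4% at 0.7 and 7.1% at 0.9 (assumed correlations, simulated).

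**Cost of adjustment.** Take the stated powers as two-sided at 0.05, and assume 0.05 also applies to the suicide outcomes. Power at a reduced level α′ is Φ(z(stated power) + 1.960 − z(1 − α′/2)).

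With one primary outcome and Holm over the other four, the first step is 0.05/4 = 0.0125, with critical value 2.498:

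- Attempts, OR 0.5: Φ(0.126 + 1.960 − 2.498) = Φ(−0.412) = 34%, against 55% stated.
- Ideation, OR 0.5: Φ(0.524 + 1.960 − 2.498) = Φ(−0.013) = 49%, taking the stated figure of over 70% as 70%.

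With Holm over all five and no single primary, the first step is 0.05/5 = 0.01, with critical value 2.576. The stated 87% becomes about 69.5%, ideation about 46% and attempts about 31%.

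These are powers at the strictest step. Later Holm steps are less strict.

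**The case against.** The strongest reply is that a statistical analysis plan may exist, that the protocol refers to further details in a clinical-trials section not shown, and that the full multiplicity procedure and the choice of scoring instrument usually belong in such places. That stands for the procedure and for the instruments. Several scales measuring the same construct are therefore not part of this point. It does not remove what the protocol itself states: a provision that places multiplicity in a sensitivity analysis, a reference to primary outcomes that are never identified, and one outcome assigned to two models.

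A second reply is that H1 speaks of the outcomes collectively, so it may require all of them. That is possible, and the 22.6% then does not apply. The figure is conditional on the any-one reading.

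A third is that the drug-use items yield both frequencies and yes/no answers, so two models for two scales are not incompatible. That also stands. The defect is that neither model is named as deciding.

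A reader might infer more than the text supports:

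- That 0.05 is fixed for every outcome. It is stated once, for continuous outcomes, without saying whether it is one- or two-sided. Unadjusted 0.05 elsewhere is the natural reading because no split is given, but it remains an inference.
- That drug misuse has three planned models. The Poisson or two-part option is a general, conditional remark about skewed outcomes and is not assigned to drug misuse.
- That a planned Poisson test would have badly wrong standard errors. The plan specifies growth models with random effects, not a single-level Poisson comparison, and the protocol gives no drug-use distribution from which overdispersion could be computed.

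**Conclusion.** The point holds as a weakness in what the protocol fixes. H1 has five outcomes without rank or decision rule, and the stated multiplicity provision leaves the main tests unadjusted. Under the any-one reading, with 0.05 for each test, the familywise error is about 22.6% if the tests are independent, about 18% at correlation 0.5, and at most 25%. Those sizes rest on the two assumptions named, and neither is written in the protocol. Separately, drug misuse has two explicit models with no stated primary, and the normal one conflicts with the expectation of skew in the same section. The documents do not show that any stated power figure is wrong.

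**What to change.** 1. In the data-preparation paragraph of section 7, replace the multiplicity sentence. Name the primary outcome or outcomes, state the alpha and whether tests are one- or two-sided, and apply a multiplicity procedure to the main H1 tests, for example a fixed order, or Holm. Which outcome is primary is the sponsor's choice. The depressive-symptom slope is one option, being the protocol's own example for its 87% power statement, though that statement covers continuous outcomes generally and does not single it out. If one primary is tested at 0.05 and the other four follow by Holm, test those four only after the primary succeeds, so that the overall error stays at 0.05.

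2. In the Aim 1 analysis text, remove drug misuse from the multivariate-normal list and make the binary growth model, on any use in the past 90 days, the deciding analysis. If use counts are also analysed, use a negative binomial or two-part growth model instead of Poisson, and label the result supportive. The two-part model is already named in the protocol.

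No new data are needed, but the change is more than editorial: it ranks Aim 1, allows fewer confirmatory claims and lowers power for the adjusted outcomes, as calculated above. The suicide outcomes lose most, from stated powers that are already modest.

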## 5) Procedures Involved\*

**Design.** To evaluate eHealth Familias Unidas Mental Health in an effectiveness-implementation hybrid Type 1 trial, this study will use a rollout design, which is an extension of a Stepped Wedge design. We will balance, and then randomize all 18 sites into five cohorts of 4 or 3 clinics to when they would end their control phase, when they would begin receiving eHealth Familias Unidas Mental Health, and when they would start the sustainability period where UM staff would no longer provide formal support (i.e., clinical supervision) to the clinic to deliver eHealth Familias Unidas Mental Health. This design is an extension of a Stepped Wedge design since it has three conditions (as shown in the figure) and provides both within and between clinic comparisons of effectiveness over time. Youth and parents will be assessed at baseline, 3-, 6-, and 18-months post-baseline. We will collect electronic health record data (e.g., exposure to an antidepressant) for participants during their control phase.

**Participants.** The sample will consist of 468 Hispanic female and male adolescents and their primary caregivers recruited from one of 18 primary care clinics, who meet the inclusion/exclusion criteria below. We will include a mix of naive and previously involved clinics in the proposed study. Because we did not attempt to institutionalize eHealth Familias Unidas in earlier involved clinics, we do not anticipate much difference in effect, but we will test for this.

A document to assess for the inclusion/exclusion criteria will be included as part of the patient check-in process. We will screen parents and adolescents separately to verify the inclusion and exclusion criteria. Adolescents will be asked questions regarding their mental health (reporting elevated depressive or anxiety symptom scores or a history of suicide behavior) and parents will be asked questions related to communication with their adolescent.

**Recruitment.** Participants will be recruited from 18 primary care clinics.

[figure not shown]

The sites are heterogeneous and consist of federally qualified health centers, academic primary care clinics located within the University of Miami's Health District, and private community clinics. Collectively, these sites jointly serve over 10,000 Hispanic between the ages of 12 -16 per year. Therefore, we do not anticipate any challenges in recruiting 468 youth over the 18-month recruitment period.

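### Blocking on clinic does not remove calendar effects in this rollout, and the Aim 1 analysis names no calendar-time term

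*Protocol*

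**What the plan says.** Protocol section 5 (Design) describes a rollout that extends a stepped wedge. The plan is to "randomize all 18 sites into five cohorts of 4 or 3 clinics to when they would end their control phase", and then to when they start the intervention and later the sustainability phase. The section presents as a strength that this "provides both within and between clinic comparisons of effectiveness over time".

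Protocol section 7 (AIM 1) then sets out growth models with "two-level modeling of clinic and individual", repeated measures lying within individuals. Its rationale is: "Since youth are recruited from all 18 clinics both during Control and eHealth Familias Unidas Mental Health", clinic can be regarded as a blocking factor, "so the overall effect is essentially a mean of the differences in response across all 18 clinics". The test is a "Wald type test on the difference in mean slope parameters for eHealth Familias Unidas versus Control assigned participants". The only time axis discussed is time since the youth's own baseline (0, 3, 6 and 18 months), because the last interval is long. The protocol names no calendar period, step, cohort or secular-trend term. Section 7 sends further detail to a Clinical Trials Section 4B, which is not part of the document.

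**The concern.** A block supports a causal contrast when condition is randomised inside it. Here condition inside a clinic is fixed by date: early enrolees are controls and later ones receive the intervention. A mean of within-clinic differences therefore compares earlier with later youth. The protection a stepped wedge offers comes from comparing, at the same calendar time, clinics that have crossed over with clinics that have not. An analysis uses that protection against calendar effects only if calendar time is in the model.

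At stake is the main effectiveness claim. A change in services, a community event or an accelerating trend in adolescent symptoms could be read as an intervention effect, or could hide one. The 18-month moderation and mediation models described under AIM 2 are exposed too. Where they compare outcome levels without baseline adjustment, even linear drift enters.

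**Working it through.** **Inputs from the protocol.** 18 clinics in five cohorts of 4 or 3; 468 youth, so 468/18 = 26 per clinic; 18-month recruitment; visits at 0, 3, 6 and 18 months; 87% power at effect size 0.5 and type I error 0.05.

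**Assumptions (not in the protocol).** Cohorts of 4, 4, 4, 3 and 3 clinics crossing over at months 3, 6, 9, 12 and 15; even enrolment; within-person correlation 0.5; clinic ICC 0.02; two-sided test; all drift sizes.

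**1. The plan's own figure.** A plain two-sample calculation with 234 per arm and effect 0.5 SD gives 99.97%, not 87%. A design effect of about 3.07 (ICC about 0.083 at 26 per clinic) would give 87%, but neither is stated. The 87% is thus neither reproduced nor shown wrong. It implies a standard error of 0.5/(1.96 + 1.126) = 0.162.

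**2. Calendar gap within a clinic.** With crossover at month c and even enrolment over 18 months, mean enrolment is at c/2 for controls and (c + 18)/2 for intervention youth. The difference is 18/2 = 9 months for any c. If each clinic instead recruits for 12 months after crossover, the gap is 7.5 to 13.5 months, mean 10.25.

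**3. Linear drift.** A drift of 0.1 SD per year adds the same slope to both conditions, so the bias in the slope contrast is 0. An unadjusted within-clinic level contrast at 18 months shifts by 0.1 x 0.75 = 0.075 SD.

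**4. Curvature.** If the level follows b x t² with b = 0.1 SD per year squared, the 18-month slope effect shifts by 2 x 0.1 x 1.5 = 0.30 SD for each year later that a youth enrols. A literal mean of within-clinic differences takes in 0.75 x 0.30 = 0.225 SD. Generalised least squares with a random clinic effect takes in 0.175 SD, because it also uses some between-clinic information.

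**5. A step of 0.3 SD at calendar month m.** Bias in the 18-month slope effect, same model:

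| m | 1 | 6 | 9 | 12 | 18 | 19 | 24 | 27 | 35 |
|---|---|---|---|---|---|---|---|---|---|
| bias (SD) | -0.02 | -0.15 | -0.19 | -0.18 | -0.04 | -0.01 | +0.18 | +0.20 | +0.02 |

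Over months 1 to 35 the mean absolute bias is 0.126 SD. At a standard error of 0.162, a bias of 0.126 gives a two-sided type I error of about 12%, 0.175 about 19%, and the maximum of 0.20 about 23%.

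**6. With calendar-quarter effects added.** The bias is 0.000 for the steps at months 12, 18, 24 and 27 (all on quarter boundaries) and below 0.001 for the curvature. The slope standard error rises by a factor of 1.28.

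**7. Power after the change.** If 87% came from a model without calendar terms, the standard error becomes 0.162 x 1.284 = 0.208, and power is Φ(0.5/0.208 - 1.96) = Φ(0.44), about 67%. Simpler clinic-by-period layouts, with ICC 0 to 0.10, inflate the variance 1.9 to 2.9 times and give 45% to 61%. A direct calculation for an outcome with SD 1, 26 youth per clinic and period effects gives about 90% to 97%.

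**The case against.** **The test is on slopes.** Each youth's own baseline is the reference, so linear drift drops out. This is correct and narrows the concern to non-linear drift, shocks and changing case-mix.

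**The multilevel model is not a pure before-after comparison.** A reader might infer from the blocking sentence that the staggering is not used at all. The stated model has clinic as a level, and with a random clinic effect it draws partly on between-clinic contrasts. It still lets calendar effects through (0.175 against 0.225 SD in step 4).

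**The large biases depend on the date of the shock.** This also stands. The sign changes with the date, some dates give almost none, and no drift size is in the document. The extremes should not be quoted as typical.

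**Details may sit elsewhere.** Section 4B or an analysis plan may contain a period term. The concern, however, is with a rationale the protocol states, and adding the term elsewhere would leave that rationale wrong.

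**The reference distribution.** With 18 clinics one might infer that the Wald test is wrongly referred to a normal distribution, since P(|t| > 1.96) is 6.7% at 17 degrees of freedom. The protocol names no reference distribution, and 17 degrees of freedom need not suit a mixed model with calendar terms. This is not a shown error.

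**Conclusion.** The concern holds for the analysis as written. Section 5 randomises crossover dates, section 7 justifies the analysis as if condition varied within clinic blocks, and nothing named removes calendar effects. Against a target of 0.5, an assumed 0.3 SD step gives a bias between about -0.19 and +0.20 SD, and curvature of 0.1 SD per year squared gives about 0.18 SD. Exactly linear drift gives none in the slope test, but does reach 18-month level contrasts without baseline adjustment. These sizes rest on the assumed crossover months, even enrolment, correlation 0.5 and ICC 0.02. The direction of the problem does not. It would go too far to infer that the trial's estimate will be biased by a known amount, or that power is certain to fall below 87%. The document supports neither.

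**What to change.** - Replace the blocking sentence in section 7. State that crossover date is the randomised element and that the effect is estimated conditional on calendar time.
- Add the calendar time of each assessment to the Aim 1 growth models, as period fixed effects or a spline common to all clinics, and keep the clinic random effect. Use the same term in the 18-month moderation and mediation models.
- If the kind of youth enrolled may change over recruitment in a way that alters slopes, also consider an enrolment-period by time-since-baseline term.
- Restate power for that model, giving the ICC and rollout schedule used.
- Optionally, specify a small-sample reference or a permutation test over the randomised rollout order.

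Cost: no new data collection should be needed, since assessments are entered electronically in REDCap. The price is precision. The slope standard error rises by about 28% in this layout, and power at 0.5 lies between about 67% (lower under other layouts) and 90% or more, depending on how the 87% was obtained. That range should be disclosed and resolved when power is restated.

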For mediation analyses, we will use the “product of coefficient” approach that we used in previous analyses to test for an indirect effect of improved family communication by 3 months, decreased externalizing behaviors by 6 months, and further decreased depressive and anxious symptoms as well as suicide ideation and attempts by 18 months. We analyze this in 2 parts, with family communication affecting externalizing followed by externalizing behaviors affecting depressive symptoms. For the second model, the product of the effect of family communication on intervention (a coefficient) and depression on family communication controlling for intervention (b coefficient) measures this latter indirect effect. We will use *Mplus* to compute bootstrapped confidence intervals since this product has a very non-normal distribution. Similarly, we will examine whether externalizing behaviors (including drug misuse) change by 6 months mediates the 18-month depressive, anxious, and suicide behavior outcomes. In addition, we propose to test whether the slope of externalizing behaviors changes on 18-month outcomes as well. To examine moderation by parental depression, we will test for an interaction with that symptomatology at baseline and intervention, both in growth models and in 18-month outcomes. We hypothesize that Familias Unidas’ effects will be moderated by parental depression with the intervention being less effective in preventing/reducing depressive, anxiety symptoms; suicide ideation and behavior and drug misuse when parents have higher depressive symptoms. Parental depression can significantly impair a person’s ability to parent as well as their family functioning and past prevention programs have found that parent depression moderates preventive intervention effects in this manner.

**Exploratory AIM 3:** Intervention impact on mental health and externalizing behaviors, including drug misuse, as well as sustainment, will vary by quality of implementation at the levels of clinic and clinician.

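### The Aim 2 product given for the externalizing step contains no externalizing term, and no test of the whole communication–externalizing–symptom chain is defined

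*Protocol*

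**What the plan says.** The Aim 2 paragraph of protocol section 7 (Data Management) opens by stating the target, an "indirect effect of improved family communication by 3 months, decreased externalizing behaviors by 6 months, and further decreased depressive and anxious symptoms", with suicide ideation and attempts added and the final outcomes placed at 18 months. That is two mediators in order and three links.

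It then says how this will be done: "We analyze this in 2 parts, with family communication affecting externalizing followed by externalizing behaviors affecting depressive symptoms". The coefficients follow. The definition starts "For the second model, the product of the effect of family communication on intervention (a coefficient" and ends with "depression on family communication controlling for intervention (b coefficient) measures this latter indirect effect". Bootstrapped confidence intervals are planned for the product.

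The next sentence adds a further analysis: "Similarly, we will examine whether externalizing behaviors (including drug misuse) change by 6 months mediates the 18-month depressive, anxious, and suicide behavior outcomes".

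Under Power Analyses in the same section, mediation power is given for one path only: "we take as an example 6-month family communication mediating 18-month depressive symptoms". With 80% power for each of a and b the product is given 64% power, and with 85% each it is given 72%.

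**The concern.** The coefficients do not match the part they are attached to. Part two is the step from externalizing to depressive symptoms. The a given for it is the intervention's effect on communication, and the b is the effect of communication on depression. Followed as written, that product would be read as evidence on the externalizing step when it carries none.

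There is also no test of the sequence the paragraph sets out to examine. Every analysis it defines has a single mediator and two links. The sequence matters to the trial's rationale: the preliminary-studies text in section 3 cites earlier evidence of exactly this cascade. A claim that the cascade has been replicated would therefore rest on models that do not estimate it.

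Finally, the only mediation power stated is for a path that leaves externalizing out and takes communication at 6 months, where the analysis takes it at 3 months.

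**Working it through.** **Step 1. Set the texts side by side** (section 7, Aim 2).

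| Item | Mediator(s) | Links |
|---|---|---|
| Stated target | communication (3 months), externalizing (6 months) | 3 |
| Part two as named | externalizing | externalizing → depressive symptoms |
| Part two as given by a and b | communication | intervention → communication; communication → depression |
| Added analysis in the next sentence | externalizing (6 months) | 2 |
| Power example | communication (6 months) | 2 |

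Externalizing is absent from the third row, and no row other than the first has three links.

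**Step 2. What each product estimates.** Write X for intervention, M1 for 3-month communication, M2 for 6-month externalizing and Y for a continuous 18-month outcome, in a linear model:

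- M1 = a1·X + e1
- M2 = a2·X + d21·M1 + e2
- Y = c·X + b1·M1 + b2·M2 + e3

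The chain is a1·d21·b2.

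- *Second model as written.* The coefficient of Y on M1 given X is b1 + d21·b2, so the product is a1·b1 + a1·d21·b2. If b2 = 0 the chain is zero, but the product is still a1·b1.
- *Externalizing as single mediator.* The effect of X on M2 is a2 + a1·d21, which includes any effect that bypasses communication. The coefficient of Y on M2 given X but not M1 is b2 + b1·d21·Var(e1) / [d21²·Var(e1) + Var(e2)]. If b2 = 0 this remains non-zero whenever b1 and d21 are non-zero, because communication then drives both externalizing and the outcome.

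So with a1, d21 and b1 non-zero and b2 = 0, the communication-to-externalizing part (a1·d21) and the externalizing single-mediator product can both be non-zero (unless a2 and a1·d21 happen to cancel), while the chain is exactly zero. The two-link pieces together do not establish the three-link effect.

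**Step 3. Reproduce the stated power.** Inputs are the per-link powers in the Power Analyses text. The rule is that power of the product equals the product of the link powers:

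- 0.80² = 0.640, stated as 64%
- 0.85² = 0.7225, stated as 72%

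Both reproduce.

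**Step 4. Extend the same rule to three links.**

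- 0.80³ = 0.512, or 51% (64.0 − 51.2 = 12.8 points lower)
- 0.85³ = 0.614, or 61% (72.25 − 61.4 = 10.8 points lower)

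To reach 80% overall, each link needs 0.80^(1/2) = 89.4% power with two links and 0.80^(1/3) = 92.8% with three.

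**Step 5. Simulation check.** With independent normal estimators, each link tested two-sided at 0.05 (an assumption; the protocol gives 0.05 for the continuous outcomes but not per link) and 4,000 replicates:

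| Power per link | Two links, all significant | Three links, all significant | Two-link product, 95% interval excludes 0 | Three-link product, 95% interval excludes 0 |
|---|---|---|---|---|
| 80% | 63.9% | 51.4% | 61.6% | 45.6% |
| 85% | 72.4% | 61.6% | 70.5% | 57.3% |

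The interval columns use a Monte Carlo interval for the product, which is closer in kind to the planned bootstrap than multiplying link powers. They run slightly lower and do not change the picture.

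**The case against.** The strongest reply is that the coefficient sentence is a drafting slip. The sentence after it does take 6-month externalizing change as a mediator of the 18-month outcomes, by the same method, so externalizing is not left out of the analysis. This stands, and it limits the harm. It does not settle the text. If that sentence is the true second model, the coefficients before it are wrong. If it is an extra analysis, the second model still lacks externalizing. Neither reading supplies a three-link product. Writing the effect of communication *on* intervention is ordinary regression-of-outcome-on-predictor phrasing and is not part of the problem.

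Several stronger readings are tempting and are not supported:

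- *That H2 itself goes untested.* H2 in section 2 names communication and externalizing behaviours as partial mediators without any order. Single-mediator tests can answer it. The order appears only in the Aim 2 analysis text.
- *That 64% and 72% are wrong, or are claimed for the cascade.* They are conditional on stated link powers, labelled an example, and correct for a two-link path. The power of the chain is unstated, and the text points to a further section, not shown, for details.
- *That the externalizing slope overlaps in time with its outcome.* The sentence "we propose to test whether the slope of externalizing behaviors changes on 18-month outcomes as well" gives no window. The four time points are stated for the Aim 1 outcome models.
- *That baseline values are wrongly omitted.* The Aim 2 text speaks of improvement and change, and covariates in mediation models are commonly left to the SAP.

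**Conclusion.** The point holds in this form: as written, the product assigned to the externalizing step is a communication-only indirect effect, and the sequence named as the target has no test of its own. Both follow from the wording of the Aim 2 paragraph and need no outside figure. The mismatch between 3-month communication in the analysis and 6-month communication in the power example is a smaller inconsistency of the same kind.

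On size, the protocol's own rule gives about 51% and 61% for three links against 64% and 72% for two, a drop of about 11 to 13 points. This extends an illustration; it does not correct an error. It assumes equal and independent links, because the protocol gives no effect size for any link. The algebra in the working is for a continuous outcome in a linear model.

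This should be corrected before analysis. It concerns a named secondary aim and does not touch the Aim 1 comparison.

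**What to change.** 1. Correct the second-model coefficients: a is intervention → 6-month externalizing, and b is 6-month externalizing → 18-month outcome given intervention. Merge this with the sentence that follows, so that it is clear whether one analysis or two is meant. If the communication-only product is also wanted, list it separately under its own name.
2. For the sequence, fit one serial model and report a1·d21·b2, where a1 is intervention → 3-month communication, d21 is 3-month communication → 6-month externalizing given intervention, and b2 is 6-month externalizing → 18-month outcome given intervention and 3-month communication. Use the bootstrap interval already planned. For suicide ideation and attempts, treated as binary under Aim 1, state a suitable link and the scale on which the indirect effect is reported.
3. In Power Analyses, use 3-month communication in the example, say that 64% and 72% apply to a two-link path only, and add that three equal, independent links would give about 51% and 61% under the same rule.

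The cost is wording and a less favourable illustrative power. No new data are needed: section 5 already has communication and externalizing measured in the assessment battery at baseline, 3, 6 and 18 months.
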